## 1. Introduction

The global burden of non-communicable diseases (NCDs) has reached unprecedented levels, with obesity and type 2 diabetes mellitus (T2DM) constituting two of the most consequential metabolic disorders of the twenty-first century. According to the World Health Organization, the worldwide prevalence of obesity has nearly doubled since 1990, with more than 890 million adults classified as obese in 2022.
^
1
^ Concurrently, the International Diabetes Federation estimates that approximately 537 million adults were living with diabetes in 2021, a figure projected to rise to 783 million by 2045.
^
2
^ These epidemiological trends are particularly alarming in the elderly population, among whom both conditions frequently co-occur and exert synergistic deleterious effects on systemic health. In India, rapid urbanization, sedentary lifestyles, and dietary transitions have accelerated the prevalence of these metabolic comorbidities, making them priority targets under the National Program for Prevention and Control of Cancer, Diabetes, Cardiovascular Diseases, and Stroke.
^
3
^

Beyond their well-established cardiovascular and metabolic sequelae, obesity and T2DM exert profound adverse effects on brain structure and function. Structural neuroimaging studies have consistently demonstrated accelerated brain atrophy, reduced grey matter volume, and compromised white matter integrity in individuals with obesity and T2DM relative to metabolically healthy controls.
^
4,
5
^ Particularly vulnerable regions include the hippocampus, prefrontal cortex, and parietal association areas, structures critically involved in memory consolidation, executive function, and visuospatial processing.
^
6
^ Diffusion tensor imaging (DTI) studies further reveal microstructural white matter disruption, evidenced by reduced fractional anisotropy (FA) and elevated mean diffusivity (MD) in major fiber tracts, consistent with demyelination and axonal loss.
^
7
^ These neuroanatomical alterations are accompanied by functional connectivity changes detectable on resting-state functional MRI, pointing to disrupted default mode and frontoparietal networks in metabolically compromised individuals.
^
8
^ Taken together, this body of evidence positions obesity associated T2DM as a significant and modifiable risk factor for accelerated neurocognitive aging.

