**2.3.1 Objectives**

The primary objective of Phase 1 is to determine and compare vascular, structural, and functional brain changes, along with alterations in cognitive function, between obese elderly adults with T2DM and those without T2DM using multimodal MR neuroimaging.

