**2.3.3 Inclusion criteria**
•Age 60–80 years, both sexes.•Clinical diagnosis of type 2 diabetes mellitus for the obese-diabetic group.•Body mass index (BMI) ≥ 25 kg/m
^2^ as per Asia-Pacific guidelines for obesity classification.
^
25
^
•Able to provide written informed consent independently or through a legally authorized representative.

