**2.3.6.2 Anthropometric and metabolic measurements**

Height will be measured to the nearest 0.1 cm using a calibrated stadiometer, and body weight will be recorded to the nearest 0.1 kg using a digital weighing scale, with participants barefoot and in light clothing. BMI will be calculated as weight (kg) divided by height squared (m
^2^). Waist circumference will be measured at the midpoint between the lowest rib and the iliac crest. Fasting blood glucose and HbA1c will be recorded from participants’ clinical laboratory reports.

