**2.3.6.7 Statistical analysis**

All statistical analyses will be performed using Jamovi. Demographic and clinical characteristics will be summarised using descriptive statistics: mean ± standard deviation (SD) for normally distributed continuous variables; median and interquartile range (IQR) for skewed data; and frequencies with percentages for categorical variables. Normality will be assessed using the Shapiro-Wilk test. Group differences in neuroimaging and cognitive outcomes will be examined using independent-samples t-tests or Mann-Whitney U tests, as appropriate. A two-way ANOVA will be used to investigate interactions between group and sex or age; a nonparametric alternative (Kruskal-Walli’s test with Dunn’s post hoc correction) will be applied when distributional assumptions are violated. Associations between neuroimaging metrics, vascular parameters, metabolic indices, and cognitive performance will be explored using Pearson’s or Spearman’s correlation coefficients and multiple linear regression models, adjusting for age, sex, years of education, and physical activity level. A significance threshold of p < 0.05 (two-tailed) will be applied throughout.

### 2.4 Phase 2

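### The Phase 1 T2DM comparison is unadjusted for degree of obesity, although BMI and waist circumference are measured in both groups

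*Protocol article*

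**What the plan says.** The Phase 1 objective (2.3.1) is a comparison "between obese elderly adults with T2DM and those without T2DM using multimodal MR neuroimaging". Obesity is meant to be common to both groups, and diabetes status is the contrast. The inclusion criteria (2.3.3) control obesity only by a floor, "Body mass index (BMI) ≥ 25 kg/m" squared. No upper limit, BMI stratum or matching on BMI is stated.

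Both adiposity measures are collected under 2.3.6.2: "BMI will be calculated as weight (kg) divided by height squared (m" squared), and "Waist circumference will be measured at the midpoint between the lowest rib and the iliac crest".

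Section 2.3.6.7 fixes the analysis:
- Group contrast: "Group differences in neuroimaging and cognitive outcomes will be examined using independent-samples t-tests or Mann-Whitney U tests, as appropriate".
- Interactions: "A two-way ANOVA will be used to investigate interactions between group and sex or age".
- Associations among imaging, vascular, metabolic and cognitive measures, described as exploratory: correlations and "multiple linear regression models, adjusting for age, sex, years of education, and physical activity level".

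Two other places name covariates. The structural MRI text in 2.3.6.4 adds total intracranial volume (TIV) to volumetric analyses. Section 2.5.10 lists age, sex, baseline physical activity, HbA1c and medication use for Phase 3. BMI and waist circumference appear in none of these lists.

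**The concern.** Sharing a lower BMI limit restricts adiposity but does not equalise it. One group can still be heavier or more centrally obese than the other. The Introduction gives a reason why this could matter: it says that inflammatory cytokines from fat tissue contribute to structural brain damage. On the plan's own reasoning, degree of obesity may therefore affect the outcomes being compared.

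If the diabetic group is heavier, an adiposity effect can be reported as a difference associated with T2DM. If it is leaner, a real difference can be masked. A single imbalance would enter several primary outcome families at once (vascular, volumetric, diffusion, connectivity), wherever the outcome is related to BMI. Agreement across modalities would then be no safeguard.

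**Working it through.** **Inputs from the protocol article.** 40 per group (2.3.5); two-tailed threshold of 0.05 (2.3.6.7); no adiposity term in the group test (2.3.6.7).

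**Inputs assumed, because the documents give neither.** D is the group difference in BMI, in within-group SDs: 0.3, 0.5 or 0.8. r is the within-group correlation of BMI with the outcome: 0.2, 0.3 or 0.4.

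**The plan's own figure.** The total of 80 in 2.3.5 contains no adiposity input, and the number of response variables in the MANOVA is not given. With f² = 0.25 and two groups, the minimum total is 78 for 11 responses and 81 for 12, so 80 is approached only at about that number. What follows uses only the 40 per group.

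**Bias in the unadjusted contrast.** With no true T2DM effect, the spurious standardised difference is d = D × r. The two-sample t-test then has noncentrality d × √(40/2) = 4.47 × d on 78 degrees of freedom. The chance of a two-sided p < 0.05 is:

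| D | r | d = D × r | 4.47 × d | False-positive rate |
|---|---|---|---|---|
| 0.3 | 0.2 | 0.06 | 0.27 | 5.8% |
| 0.5 | 0.3 | 0.15 | 0.67 | 10.2% |
| 0.8 | 0.4 | 0.32 | 1.43 | 29.3% |

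**Simulation of the same three cases (3,000 runs).** The unadjusted test rejected in 6.5%, 9.5% and 28.6% of runs. With BMI in the model, it rejected in 5.3%, 4.6% and 5.4%.

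**Second simulation (4,000 runs)** at D/r of 0.5/0.3, 0.8/0.3 and 0.5/0.5. Unadjusted rejection was 10.8%, 18.4% and 19.6%. With BMI as a covariate it was 4.2% to 5.0%, and the remaining bias was at most 0.006 SD.

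**Wider range.** Over D of 0.2 to 0.8 and r of 0.1 to 0.5, d runs from 0.02 to 0.40 and the false-positive rate from 5.1% to 42.4%. At D = 0 or r = 0 the bias is zero and the rate is 5%.

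**Scale.** The smallest difference detectable with 80% power at 40 per group is d = 0.63. The largest of the three headline biases is about half of that (0.32/0.63 = 0.51), and the smallest about a tenth (0.06/0.63 = 0.10).

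**The case against.** The strongest reply is that Phase 1 is described as a comparison and characterisation of two clinical groups, not as an estimate of the causal effect of T2DM, so the choice of adjustment set is partly a matter of judgement. BMI is also measured after diabetes onset. The cytokine pathway in the Introduction runs partly through insulin signalling, a mechanism shared with T2DM, so BMI is not purely a confounder. This stands as a reason to show both estimates. It is not a reason to show only the unadjusted one.

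A second reply is that the Introduction's statement "Structural neuroimaging studies have consistently demonstrated accelerated brain atrophy, reduced grey matter volume, and compromised white matter integrity in individuals with obesity and T2DM" compares such people with metabolically healthy controls. It does not show a graded adiposity effect among people who are all obese. That is correct, so the r values above remain assumptions.

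Third, the metabolic indices in the association analyses might include BMI, and the descriptive summary might reveal an imbalance. Neither would remove an imbalance from the group contrast, and a covariate chosen after seeing the imbalance would be post hoc.

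A reader might also infer more than the documents support:
- *That adding BMI to the quoted covariate list would solve the problem.* That list governs the association regressions; the group contrast would stay unadjusted.
- *That the groups will be unbalanced.* The article states no matching, but it is a condensed account and gives no evidence that adiposity will differ.
- *That part of every reported difference is an adiposity effect.* Bias arises only where the groups differ in BMI and the outcome is related to it.

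**Conclusion.** The point holds in conditional form. As written, the plan lets any group difference in degree of obesity pass into the Phase 1 T2DM contrast for outcomes related to BMI, and no stated design feature beyond the shared floor prevents it. This is not detail left to an analysis plan, because the article itself names the tests and the covariates.

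The size cannot be taken from the documents. Under the assumed range it is about 0.06 to 0.32 SD, with a false-positive rate per outcome of about 6% to 29%. The upper figure pairs the largest assumed imbalance with the largest assumed correlation and should not be read as the expected value. The change is worth making because the data will be collected anyway and the Data Availability statement says that no participant data exist yet, so it can still be prespecified.

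**What to change.** In 2.3.6.7, make the main analysis of each Phase 1 group comparison a linear model (ANCOVA) of the outcome on group, with age, sex, years of education, physical activity level and baseline BMI, plus TIV for volumes. Then:
- report the group estimate with and without BMI;
- repeat the model with waist circumference in place of BMI as a sensitivity analysis;
- tabulate BMI and waist circumference by group.

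In the association regressions, add BMI only where neither BMI nor waist circumference is the predictor under study; otherwise the question changes.

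**Cost.** No new measurement. With one term per covariate, the model has seven parameters including the intercept, leaving 80 − 7 = 73 residual degrees of freedom (72 with TIV) against 78 for the t-test. The change replaces the test and is more than one extra covariate, but the TIV requirement already calls for a covariate-adjusted group model for volumes. The downside is possible over-adjustment if T2DM or its treatment altered weight, which is why both estimates are shown.

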**2.3.5 Sample size**

Sample size was estimated using G*Power 3.1 software. A multivariate analysis of variance (MANOVA) power analysis was performed with an assumed medium effect size (f
^2^ = 0.25), a significance level of α = 0.05, and a desired statistical power of 0.80. This yielded a minimum total sample of 80 participants. Accounting for anticipated attrition and protocol deviations, 40 participants will be recruited to each group (obese-diabetic and obese-non-diabetic), yielding a total of 80 participants for Phase 1.

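### The covariate list for the exploratory Phase 1 association models omits diabetes group, so between-group differences alone can produce significant associations, most of all for HbA1c and glucose

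*Protocol article*

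**What the plan says.** Section 2.3.6.7 (Statistical analysis, Phase 1) states: "Associations between neuroimaging metrics, vascular parameters, metabolic indices, and cognitive performance will be explored using Pearson’s or Spearman’s correlation coefficients and multiple linear regression models". The adjustment set for these analyses is then given in the same sentence as "adjusting for age, sex, years of education, and physical activity level". One criterion covers everything in that section: "A significance threshold of p < 0.05 (two-tailed) will be applied throughout".

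Diabetes group appears elsewhere in that section, in the t-tests or Mann-Whitney tests and in the factorial model: "A two-way ANOVA will be used to investigate interactions between group and sex or age". It is not in the covariate list for the association models. Section 2.3.6.4 adds intracranial volume as a covariate for volumetric analyses. No section adds group or describes associations estimated within each group.

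The sample is fixed by design (section 2.3.5): "40 participants will be recruited to each group (obese-diabetic and obese-non-diabetic), yielding a total of 80 participants for Phase 1". What separates the groups is a diagnosis (section 2.3.3): "Clinical diagnosis of type 2 diabetes mellitus for the obese-diabetic group". The metabolic indices include the markers of that diagnosis (section 2.3.6.2): "Fasting blood glucose and HbA1c will be recorded from participants’ clinical laboratory reports".

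**The concern.** Participants are selected on diabetes status in a 1:1 ratio. HbA1c and fasting glucose will differ between the groups almost by definition. The study's premise, set out in the Introduction and section 2.3.1, is that vascular, brain and cognitive measures may differ too. When two variables both have different group means, combining the groups creates a correlation between them, whatever happens inside each group. None of the four listed covariates is diabetes status, so they remove the artefact only so far as they happen to differ by group themselves.

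At stake is how an HbA1c-brain or vessel-brain result can be read. A significant coefficient could reflect a relation among people of the same diabetes status, or it could restate the group comparison that is already tested separately. With the listed covariates the reader cannot tell which.

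**Working it through.** **The plan's own figures.** The protocol gives no expected correlation or group separation for these analyses, so there is no figure to reproduce for this point. Its total of 80 comes from a MANOVA calculation whose number of response variables is not stated. With f² = 0.25, 10 responses need 75 participants and 12 need 81, so 80 cannot be confirmed. Nothing below depends on it beyond the group sizes.

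**Inputs from the protocol.** 40 + 40 participants; two-sided 0.05; covariates age, sex, education and physical activity; no group term.

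**Assumed inputs.** Within-group association zero. Group separations in within-group SD units: dx for the predictor, dy for the outcome. The listed covariates are simulated as unrelated to group. The value 0.63 SD is what a single two-sample comparison of 40 + 40 detects with 80% power: (1.96 + 0.84) × √(2/40) = 0.63.

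**Step 1: induced correlation.** With 1:1 groups the between-group covariance is dx·dy/4, and each total variance is 1 + d²/4. So

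r = (dx·dy/4) / √[(1 + dx²/4)(1 + dy²/4)].

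For dx = 2 and dy = 0.63: 0.315 / √(2 × 1.099) = 0.21. The critical |r| at n = 80 is 0.22, so in this setting the group difference alone takes the test to about an even chance of significance.

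**Step 2: rejection rates by simulation** (thousands of data sets per setting; at 4,000 runs, simulation error is at most about ±1.5 points).

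| dx (SD) | dy (SD) | induced r | four listed covariates |
|---|---|---|---|
| 2 | 0 | 0.00 | 5% |
| 0.5 | 0.5 | 0.06 | 8% |
| 0.63 | 0.63 | 0.09 | 12% |
| 1 | 0.5 | 0.11 | 16% |
| 2 | 0.3 | 0.11 | 15% |
| 2 | 0.5 | 0.17 | 33% |
| 1.5 | 0.63 | 0.18 | 37% |
| 2 | 0.63 | 0.21 | 46% |
| 3 | 0.63 | 0.25 | 61% |

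The rows with dx up to 1 stand for vessel-brain type pairs; those with dx of 1.5 to 3 stand for HbA1c or glucose. Unadjusted Pearson tests give slightly higher rates (34.5% against 32.6% at 2 by 0.5 SD). With a group term added, the rate is about 5% in every setting.

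**Step 3: cost of the group term for HbA1c.** The variance inflation of the HbA1c slope is the ratio of total to within-group variance, 1 + dx²/4:

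- 1.5 SD: 1 + 2.25/4 = 1.56
- 2 SD: 1 + 4/4 = 2.00
- 3 SD: 1 + 9/4 = 3.25

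If HbA1c truly related linearly to the outcome with an overall r of 0.30, power at n = 80 would fall from about 79% without the group term to about 59%, 48% or 33% with it.

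**The case against.** **Pooling is not stated.** The section never says that the two groups are combined, and a condensed article may leave that to the full plan. This stands as a caution. But one set of models, one explicit covariate list and no mention of stratification, in a two-group phase, make pooling the plain reading. The covariate list is stated, not left open.

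**The analyses are exploratory.** They are described as explored, and no association is listed as a primary or secondary outcome. The Phase 1 objective is the group comparison, which has its own tests. This stands and sets the priority. It does not remove the point, because the 0.05 threshold applies here too.

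**Rejecting a zero overall correlation is not strictly an error.** If both variables differ by group, the correlation across the whole sample is truly non-zero. This stands: the rates above are errors only about a within-group association, so the fault lies in what the result can be taken to show.

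**For HbA1c, group is not a clean confounder.** Diabetes status is itself defined by glycaemia, so conditioning on it removes much of the exposure contrast and, as step 3 shows, much of the power. This stands, and it is why the group-adjusted model should not simply replace the unadjusted one for these markers.

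**Stronger readings.** A reader might infer that the Phase 1 associations merely retest the group difference, that vessel-brain results are as badly affected as HbA1c results, or that the investigators will present them as dose-response relations. The documents support none of these. A combined coefficient also carries any real within-group association. Vessel-brain inflation is modest at moderate separations. The protocol does not say how the results will be worded.

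**Conclusion.** The point holds in a limited form. The stated adjustment set for the Phase 1 association models lacks diabetes group. If the groups are analysed together, as the text most naturally reads, differences in group means can produce significant associations with none inside either group.

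The size rests on separations the protocol does not give. The inflation is negligible where either variable differs little by group and modest for vessel-brain type pairs. It can be large for HbA1c and glucose, but only if the imaging measure also differs by group. Listed covariates that are themselves related to group would remove part of it. The primary group comparisons are unaffected. This is a lower-priority improvement to an exploratory analysis.

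**What to change.** In section 2.3.6.7, or in the full analysis plan:

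1. State whether the Phase 1 associations are estimated across both groups, within groups, or both.
2. Add diabetes group to the covariate list for the vascular-brain, brain-cognition and vascular-cognition models.
3. For HbA1c and fasting glucose, report the model with and without the group term, or give within-group estimates beside the combined one. Label the combined result as including the between-group difference, and not as evidence of a glycaemic gradient within groups.
4. Say that a null group-adjusted slope for HbA1c or glucose will not be read as absence of a relation, given its imprecision.

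The cost is a few sentences. Group is already recorded, and the Data Availability section says that no participant data have been collected. The one statistical price is the loss of precision for the glycaemic markers shown in step 3, which reporting both versions makes visible.

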**2.3.6.3 Vascular assessment: carotid doppler ultrasonography**

Carotid Doppler ultrasonography will be performed with participants seated following a 10-minute rest period. A 7–15 MHz multifrequency linear array transducer will be used with a high-resolution B-mode ultrasound machine. Peak systolic velocity (PSV), end-diastolic velocity (EDV), and resistive index (RI) of the common carotid artery (CCA) will be recorded bilaterally. Carotid artery diameter will be measured at the far wall of the CCA, 1 cm proximal to the carotid bifurcation. Endothelial shear stress will be calculated from the velocity and diameter values. All measurements will be performed by the same trained sonographer throughout the study to minimize inter-rater variability. A minimum of three consecutive cardiac cycles will be averaged for each measurement.

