**Sequence 1: Structural MRI — Volumetric brain morphometry**

A T1-weighted three-dimensional Fast Spoiled Gradient Echo (FSPGR) sequence will be acquired for voxel-based morphometry (VBM) analysis. Imaging parameters will include repetition time (TR) = 7.8 ms; echo time (TE) = 3.1 ms; inversion time (TI) = 1010 ms; flip angle = 10°; field of view (FOV) = 256 × 256 mm; voxel size = 1 × 1 × 1 mm isotropic; 176 contiguous axial slices. Post-processing and analysis will be performed in MATLAB (MathWorks) using the SPM12 toolbox (Wellcome Centre for Human Neuroimaging, UCL) with the CAT12 (Computational Anatomy Toolbox, version 12) extension.
^
28
^ The standard CAT12 cross-sectional pipeline will be applied, comprising: (1) bias-field correction and denoising; (2) unified segmentation into grey matter (GM), white matter (WM), and cerebrospinal fluid (CSF) tissue classes; (3) diffeomorphic registration to the MNI152 standard space using the Geodesic Shooting algorithm (DARTEL); and (4) modulation of segmented images to preserve absolute tissue volumes following normalisation. For ROI-based segmentation, the CAT12 automated parcellation will be applied using the Automated Anatomical Labeling (AAL3) atlas, extracting absolute and relative grey matter volumes for bilateral regions of interest, including the hippocampus, entorhinal cortex, prefrontal cortex, anterior cingulate cortex, insula, and parietal association cortex. Total intracranial volume (TIV) will be extracted from the Jacobian determinant maps and used as a covariate in all volumetric analyses to account for individual differences in head size.

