**Sequence 2: Diffusion tensor imaging (DTI)**

White matter microstructural integrity will be assessed using a single-shot echo-planar DTI sequence acquired with participants in the supine position. Acquisition parameters will include TR = 4237 ms; TE = 87.3 ms; b-values = 0 and 1000 s/mm
^2^; 32 non-collinear diffusion gradient directions; FOV = 220 × 220 mm; voxel size = 1.72 × 1.72 × 2 mm; 45 axial slices; and GRAPPA acceleration factor = 2. DTI data will be pre-processed and analyzed using ExploreDTI.
^
29
^ Pre-processing will include: (1) signal drift correction; (2) Gibbs ringing suppression; (3) eddy current and subject motion correction using a robust tensor estimation approach with outlier rejection (REKINDLE algorithm); and (4) brain extraction. The diffusion tensor will be estimated at each voxel using a non-linear least squares fitting procedure. ROI-based tractography will be performed using deterministic streamline tractography (Euler integration, step size = 1 mm, FA threshold = 0.20, maximum turning angle = 30°). White matter tracts of primary interest — including the corpus callosum, corticospinal tract, superior longitudinal fasciculus, inferior fronto-occipital fasciculus, cingulum, and uncinate fasciculus — will be reconstructed using atlas-based ROI placement guided by the JHU white matter atlas. Mean values of fractional anisotropy (FA), mean diffusivity (MD), radial diffusivity (RD), and axial diffusivity (AD) will be extracted per tract per participant for between-group and pre-post comparisons.

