**Sequence 3: Resting-State functional MRI (rs-fMRI)**

Resting-state BOLD (Blood Oxygenation Level-Dependent) fMRI will be acquired using a gradient-echo echo-planar imaging (EPI) sequence. Parameters: TR = 3000 ms; TE = 30 ms; flip angle = 80°; FOV = 230 × 230 mm; voxel size = 3.5 × 3.5 × 3.5 mm; 40 interleaved axial slices. Participants will be instructed to lie still with eyes open, fixated on a cross projected on a screen, and to refrain from deliberate mental activity. RS-fMRI data will be preprocessed using the CONN toolbox (v22.a) in MATLAB, including slice-timing correction, realignment, co-registration to T1 structural image, normalization to MNI space, and spatial smoothing (6 mm FWHM Gaussian kernel).
^
30
^ Independent component analysis (ICA) will be used to identify and remove noise components (motion, physiological artifacts). Default mode network (DMN), frontoparietal network (FPN), and salience network (SN) connectivity will be examined as primary functional outcomes using seed-based and ICA-based approaches.

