**2.3.6.6 Outcome measures**

**Primary outcomes**
•Carotid artery and superficial femoral artery diameter, PSV, EDV, RI, and endothelial shear stress (Doppler ultrasonography).•Regional grey matter volume and TIV (T1-weighted VBM).•FA, MD, RD, and AD of major white matter tracts (DTI).•Resting-state functional connectivity of the DMN, FPN, and SN (rs-fMRI).

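### Phase 1 tests about 39 or more primary comparisons one at a time at an unadjusted 0.05, with no lead measure, so the familywise error is far above 5%

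*Protocol article*

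**What the plan says.** Section 2.3.6.6 lists four families of primary outcomes for Phase 1 and ranks none of them.

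- **Vascular:** "Carotid artery and superficial femoral artery diameter, PSV, EDV, RI, and endothelial shear stress (Doppler ultrasonography".
- **Volume:** regional grey matter volumes and TIV. The imaging section names the regions: "including the hippocampus, entorhinal cortex, prefrontal cortex, anterior cingulate cortex, insula, and parietal association cortex". It extracts them on both sides, as absolute and as relative volumes.
- **Diffusion:** "Mean values of fractional anisotropy (FA), mean diffusivity (MD), radial diffusivity (RD), and axial diffusivity (AD) will be extracted per tract per participant", with six tracts named.
- **Connectivity:** three networks (DMN, FPN, SN), which "will be examined as primary functional outcomes using seed-based and ICA-based approaches".

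Section 2.3.6.7 sets the test: "Group differences in neuroimaging and cognitive outcomes will be examined using independent-samples t-tests or Mann-Whitney U tests, as appropriate". It then sets the threshold: "A significance threshold of p < 0.05 (two-tailed) will be applied throughout". The only correction it names belongs to the non-parametric substitute for the two-way ANOVA: "test with Dunn’s post hoc correction) will be applied when distributional assumptions are violated".

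Section 2.3.5 bases the sample size on a MANOVA, but section 2.3.6.7 contains no MANOVA. For Phase 3, section 2.5.9 repeats the four families as primary. Section 2.5.10 gives paired tests and mixed models, with neither a significance threshold nor a correction.

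On the Doppler procedure, section 2.3.6.3 says: "Peak systolic velocity (PSV), end-diastolic velocity (EDV), and resistive index (RI) of the common carotid artery (CCA) will be recorded bilaterally". Diameter is also described for that artery only.

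**The concern.** When dozens of outcomes are all primary and each is judged alone at 0.05, a few will usually cross the line even if diabetes status makes no difference to any of them. Nothing in the plan says which result would count as the main finding, so any of them could be reported as one. This matters because the discussion expects confirmed benefits to feed into prevention programmes and clinical guidelines.

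This is not a detail left to an analysis plan. The article states the threshold and its scope, and an analysis plan that adjusted for multiplicity would contradict it.

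The femoral artery is a separate matter: a primary outcome without a described measurement leaves the content of the vascular family open.

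**Working it through.** **1. The plan's own figure.** The article states no familywise error rate and no number of primary tests. Its only related figure is N = 80 from the MANOVA (f² = 0.25, α = 0.05, power 0.80). With a two-group global test (df1 = p, df2 = N − p − 1, noncentrality N·f²), N depends on the number of response variables p, which is not given:

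| p | Required N |
|---|---|
| 1 | 34 |
| 4 | 53 |
| 11 | 78 |
| 12 | 81 |
| 39 | 139 |

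So 80 corresponds to about 11 or 12 response variables, far fewer than the primary list contains.

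**2. Count of primary comparisons in Phase 1.**

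| Family | Named measures, carotid only | All splits, carotid only |
|---|---|---|
| Doppler | 5 | 5 × 2 sides = 10 |
| Volumes | 6 regions + TIV = 7 | 6 × 2 sides × 2 volume types + TIV = 25 |
| Diffusion | 6 tracts × 4 metrics = 24 | 11 tracts × 4 = 44 |
| Connectivity | 3 networks | 3 × 2 approaches = 6 |
| **Total** | **39** | **85** |

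The femoral artery adds 5 to the first total (44) and 10 to the second (95). The right-hand column is an assumption: the article does not say that each split is a separate primary test, and the 11 tracts come from splitting all but the corpus callosum by side.

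**3. Expected false positives if every null is true.** This is m × 0.05 and does not depend on correlation.

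- 39 × 0.05 = 1.95
- 44 × 0.05 = 2.20
- 85 × 0.05 = 4.25
- 95 × 0.05 = 4.75

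**4. Chance of at least one false positive.** Under independence it is 1 − 0.95^m. For correlated tests I used a simulation with four equicorrelated blocks (100,000 runs). The correlations are assumed, since the article gives none.

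| m | Independent | 0.3 within, 0.1 between | 0.5 within, 0.1 between | 0.9 within, 0.1 between |
|---|---|---|---|---|
| 39 | 86.5% | 79% | 70% | 39% |
| 44 | 89.5% | 83% | 73% | 40% |
| 85 | 98.7% | 95% | 87% | 47% |
| 95 | 99.2% | 97% | 90% | 48% |

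**5. Is there a safeguard elsewhere?** Dunn's correction acts between groups within one outcome, not across outcomes. The MANOVA is not in the analysis section, so it cannot serve as a gatekeeper.

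**6. The femoral artery across sections.** Section 2.3.6.6 lists it as primary. Section 2.3.6.3 describes only the common carotid, section 2.5.9 names only carotid haemodynamics, and the abstract and discussion mention only carotid Doppler.

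**The case against.** The strongest reply is that the tests are far from independent. FA, MD, RD and AD come from one tensor fit, the two sides of the brain are related, and absolute and relative volumes express the same region. That stands, and it lowers the familywise error considerably. It does not change the expected number of false positives, and the lowest familywise error obtained, 39%, is still about eight times 5%.

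Some stronger readings are tempting but not supported:

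- **That a false-positive primary result is close to certain.** Only the upper counts under independence (about 99%) come near this, and every such figure assumes that no true difference exists.
- **That these are co-primary outcomes.** The article does not use the term. Strictly it means that all must succeed, which does not inflate the error. These are multiple primary outcomes.
- **That the femoral artery is never scanned.** The article is condensed, and one can say only that it describes no femoral scan. If there were none, its tests would yield no p-values, so the carotid-only counts are the safer ones.
- **That Phase 3 is stated to use an unadjusted 0.05.** The threshold sentence sits in the Phase 1 section. Carrying it to Phase 3 rests on its word throughout.
- **That voxel-wise maps will be thresholded at 0.05.** The article states no threshold for maps, so this is not part of the point.

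The region and tract lists open with the word including, so neither 39 nor 95 is a strict bound.

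**Conclusion.** The point holds for Phase 1. The article explicitly fixes single-outcome tests at an unadjusted two-sided 0.05 for about 39 named primary comparisons (carotid only) and possibly about 85, with no lead measure and no correction across outcomes. If no true differences exist, about 2 to 4 false-positive primary results are expected. The familywise error is 86.5% or more if the tests are independent, about 70% at 39 tests with the middle correlation assumption, and about 39% in the most favourable case tried. The higher counts rest on assumed splits and the correlated figures on assumed correlations. No choice of these brings the error near 5%.

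For Phase 3 the same problem is a reasonable inference, not stated text. The femoral entry is a separate inconsistency between the outcome list and the described procedure. It needs reconciling but does not drive the error rate.

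**What to change.** 1. Before data collection, replace the blanket 0.05 with a prespecified multiplicity rule. One workable form names a single primary measure in each domain (vascular, volume, diffusion, connectivity) and tests the four with Holm at 0.05. All other measures become secondary, with Benjamini-Hochberg FDR within domain. Other rules would also serve, such as a MANOVA gatekeeper consistent with section 2.3.5, provided the response variables are named.
2. State in section 2.5.10 that the same rule applies to Phase 3.
3. Make sections 2.3.6.3, 2.3.6.6 and 2.5.9 agree on the superficial femoral artery, either by removing it from the primary list or by describing its acquisition.

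**Cost.** At the first Holm step (0.05/4 = 0.0125), the effect detectable with 80% power and 40 per group rises from d = 0.63 to d = 0.76. This is milder than Bonferroni over 39 tests (0.05/39 = 0.00128), where it would be d = 0.94. These figures are for Phase 1 only. The trial is already registered, so the outcome list needs an amendment there as well as new wording. The article says that no participant data had been collected at publication, so the change could still be made before any results are known.
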